#### **Analysis strategy**

The purpose of the analysis is to describe changes in sales volume of meat products and meat-free alternatives and to test for differences in sales volume between the intervention and control stores, adjusted for differences in sales volume during the pre-intervention comparator period. The analysis will also adjust for store characteristics found to be potential confounders in the preliminary analysis.

Prior to analysing the primary and secondary outcome data, we will run the analysis for control outcome measures (e.g. fish and non-dairy milk sales) to check that sales of these two products do not differ between intervention and control stores, after adjusting for pre-intervention sales and store characteristics.

The main analysis will be conducted using all intervention and control stores. If the two groups are found not to be comparable with regard to time trends, we may additionally perform a subgroup analysis based on stores considered to be comparable. Other exploratory analyses may be conducted but will be described as *post hoc* in the study reports.

### Statistical methods

For all outcomes, we will report the number and percentage of observed values, mean and standard deviation, median and inter-quartile range, and range, by arm (intervention vs control) and for the full sample, and by time period (intervention period vs pre-intervention comparator period). The outcome measure (mean weekly units sales) is a count outcome thus analysis will be performed using regression models that deal with count outcomes.

We will use conditional regression to account for the matching of stores. Univariate associations between baseline characteristics (pre-intervention period sales) and outcome (intervention period sales) will be examined with the use of conditional negative binomial regression. Multivariate analysis will be conducted using conditional negative binomial regression adjusted for the covariates (store characteristics) and also the baseline count (pre-intervention period sales)[11].

Results will be presented as incident-density ratios with 95% confidence intervals and p-values. For this pilot study, all statistical tests will be conducted at a 5% significance level, but interpretation of findings for secondary outcomes will be based on consistency of findings in recognition of the risk of false positives associated with multiple testing.

In the event that some stores are selected as control stores for multiple intervention stores, we will run the analysis on the full dataset and conduct a sensitivity analysis to assess whether this affects the findings. If appropriate, duplicates will be removed and the analysis re-run using only unique control stores.

In addition use of interrupted time series will be considered depending on the nature and availability of data in order to examine the effectiveness of the intervention [12].

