## Outcome measures

Two measures of sales are available – number of units sold and sales revenue (£) for the product categories of interest. Our primary focus will be on changes in units sold.

Average weekly sales (units and £) will be calculated as the average of weekly sales for the relevant study period i.e. either the comparator or intervention period

In order to be able check that any changes in purchasing are attributable to the intervention and not to confounding, we will also evaluate sales of two products (fresh fish and non-dairy milks) which should be unaffected by the intervention in both intervention and control stores.

All outcome measures are based on sales of the 26 stock keeping units (SKUs) that have been moved into the MFP aisle and on the meat product equivalents.

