### Primary outcomes

- Average total weekly sales (Units) of mince, burgers, meatballs and sausages (meat)

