### Secondary outcomes

- Average weekly sales (Units and £) per store of mince (meat)
- Average weekly sales (Units and £) per store of burgers (meat)
- Average weekly sales (Units and £) per store of meatballs (meat)
- Average weekly sales (Units and £) per store of sausages (meat)
- Average total weekly sales (£) of mince, burgers, meatballs and sausages (meat)
- Average weekly sales (Units and £) per store of meat-free alternative mince
- Average weekly sales (Units and £) per store of meat-free alternative burgers
- Average weekly sales (Units and £) per store of meat-free alternative meatballs
- Average weekly sales (Units and £) per store of meat-free alternative sausages
- Average total weekly sales (Units and £) of meat free alternative mince, burgers, meatballs and sausages

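### An average of weekly unit sales is called a count and given a negative binomial model, which makes standard errors too large for low-volume products

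*Protocol*

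**What the plan says.** Protocol, Outcome measures, defines the quantity to be analysed: "Average weekly sales (units and £) will be calculated as the average of weekly sales for the relevant study period". The primary outcome is "Average total weekly sales (Units) of mince, burgers, meatballs and sausages (meat"). The secondary outcomes include single product lines, for example "Average weekly sales (Units and £) per store of meat-free alternative meatballs", and revenue, for example "Average total weekly sales (£) of mince, burgers, meatballs and sausages (meat").

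Protocol, Statistical methods, then states "The outcome measure (mean weekly units sales) is a count outcome" and gives this as the reason for using count regression. The adjusted model is set out as "Multivariate analysis will be conducted using conditional negative binomial regression adjusted for the covariates (store characteristics") "and also the baseline count (pre-intervention period sales"), with a reference whose title shows that it compares ways of entering baseline counts in negative binomial models. Whether baseline enters raw or logged is not stated. No other regression model is named for any outcome, apart from a possible interrupted time series. Annex A asks for one row per store and week.

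**The concern.** The two sections do not fit together. Weekly unit sales are counts, and so is their total over a period. Their average is not: it takes fractional values, and its sampling variance is far smaller than a count model allows. Because the model is justified by the count label, this is a stated rule that is wrong, not a detail left for later.

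The second half of the research question is at stake: whether sales of meat-free alternatives rise. The single meat-free categories are the most likely to sell in small numbers per store, and there a real increase could be missed. Secondary outcomes are to be read by consistency across products, and that reading suffers if precision depends on how the outcome was scaled.

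Two related points sit in the same paragraph: the unstated form of the baseline term, and the absence of a suitable model for revenue.

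**Working it through.** The protocol gives no sales volumes, variances or power figure, so there is no figure of its own to reproduce. From the protocol come 20 intervention stores, five matched controls each, and nominal 12-week periods. All volumes and variances below are assumptions.

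**1. Variance of the average.** Let mu be a store's expected weekly units, and CV the extra variation of a store from period to period. With Poisson weekly counts, the average of 12 weeks has variance V = mu/12 + CV²·mu². A negative binomial has variance mu + alpha·mu² with alpha ≥ 0, so never below mu. Where V < mu, the standard error is inflated by sqrt(mu/V). Where V ≥ mu, alpha absorbs the excess and the ratio is 1.

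| mu per week | CV 0.05 | CV 0.10 | CV 0.20 |
|---|---|---|---|
| 5 | 3.2 | 2.7 | 1.9 |
| 20 | 2.7 | 1.9 | 1.1 |
| 100 | 1.7 | 1.0 | 1.0 |
| 500 or more | 1.0 | 1.0 | 1.0 |

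Example: mu = 5 and CV = 0.10 give V = 0.417 + 0.250 = 0.667, and sqrt(5/0.667) = 2.7. The problem ends where V = mu, that is at mu = (11/12)/CV²: 367, 92 and 23 units a week for the three CVs. The ceiling, with CV = 0, is sqrt(12) = 3.5.

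**2. Noise in the baseline.** Step 1 treats baseline as known. If baseline is equally noisy and enters with slope near 1, the true variance doubles and the ratio falls by sqrt(2). With CV = 0.08, mu = 5 gives V = 0.417 + 0.160 = 0.577 and a ratio of sqrt(5/1.153) = 2.1. For mu = 20, V = 1.667 + 2.560 = 4.227 and the ratio is sqrt(20/8.453) = 1.5.

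**3. Simulation.** 20 sets of 1:5, no true effect, CV 0.08, between-set log-SD 0.5, within-set log-SD 0.2 or 0.5, no baseline imbalance, 60 runs per setting. Negative binomial likelihood with matched-set indicators stood in for the conditional model.
- Averages, log baseline: model SE over empirical SD was 1.9 to 2.0 at 5 units a week, with no rejections in any run, and 1.4 to 1.5 at 20.
- Averages, raw baseline: 1.4 to 1.95 at 5 a week and 0.86 to 1.36 at 20. Lack of fit from the raw term can mask the inflation.
- Totals, log baseline: 0.77 to 0.93 at 5 a week and 0.89 to 1.11 at 20.
- At 1500 a week and within-set SD 0.3, averages and totals give the same SE, 0.0245.

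A separate simulation with the conditional likelihood itself, again on assumed volumes, gave ratios of 2.3, 2.1, 1.7, 1.2 and 1.0 at 3, 5, 10, 30 and 200 units a week.

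What this could cost: take a true 20% rise at 5 a week, log(1.2) = 0.182, with empirical SD 0.055 and model SE 0.104. The estimate must exceed 1.96 × 0.104 = 0.203, so power is P(Z > (0.203 − 0.182)/0.055 = 0.38), about 35%. With a correct SE the threshold is 0.108 and power is about 91%.

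**4. Form of the baseline term.** At 1500 units a week and no true effect:

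| Within-set SD | Ratio, 0.2 log imbalance: raw / log | Empirical SD, no imbalance: raw / log |
|---|---|---|
| 0.1 | 1.110 / 1.083 | 0.024 / 0.023 |
| 0.3 | 1.049 / 1.011 | 0.042 / 0.026 |
| 0.5 | 1.034 / 0.999 | 0.061 / 0.028 |

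With no imbalance neither form is biased (ratios 0.997 to 1.004).

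**5. Revenue.** The relative variance under a negative binomial is 1/mu + alpha, and the first term depends on the currency unit. At an assumed mean of £20 it cannot go below 1/20 = 0.05. In pence the same data have a floor of 1/2000 = 0.0005. One simulated data set gave SE 0.066 in pounds and 0.046 in pence.

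**The case against.** The strongest reply is that this is loose wording with little consequence. The error is conservative, it fades as volume rises, and the primary outcome pools four meat categories per store, where volumes are probably high. The protocol makes no power claim and reads secondary outcomes for consistency. All of that stands and limits the point. It does not rescue the sentence, which gives a wrong premise as the reason for the model.

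Three stronger readings are tempting, and the protocol does not support them.
- A reader might infer that revenue is declared a count. It is not: the sentence names units only. The fair point is that no other model is offered for £.
- A reader might infer that baseline enters untransformed. The text leaves the form open and cites a source on that very choice.
- A reader might infer that the primary meat result is confounded. That would need both a raw baseline term and a difference in meat sales within matched sets. Such a difference is plausible, since matching used meat-free purchasing and did not require spare space in the control stores. It is not shown, and the protocol plans to check pre-intervention trends for both product groups and allows control selection to change.

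It is also fair to say that the remedies are partial. A log baseline still left a ratio of 1.083 at small within-set spread. Model-based standard errors on low-volume totals ran somewhat small, although 60 runs is a noisy basis. This is why robust standard errors belong in the fix.

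**Conclusion.** The point holds for unit outcomes with low sales: the protocol mislabels an average as a count, and the model that follows cannot represent its variance. Standard errors would be about 2 to 3 times too large at 5 units a week, 1.1 to 2.7 times at 20, and unaffected at several hundred. The simulations fall at or near the lower end at 5 a week and mid-range at 20. The direction is conservative, so the risk is missed effects on small meat-free lines, not false ones.

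These sizes rest on assumed volumes, Poisson variation between weeks and CVs of 0.05 to 0.20. More week-to-week variation, for instance from promotions, would shrink the inflation. The protocol does not show that any category sells as little as 5 or 20 a week, so a reader should not conclude that the meat-free outcomes do lose most of their power. Nor should a reader conclude that the primary result is wrong: its standard error is probably unaffected.

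The baseline form and the revenue model are matters to state clearly. They are not demonstrated errors.

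**What to change.** Rewrite the modelling paragraph in Statistical methods:
- **Units.** Analyse each store's total over the intervention period, or its weekly counts, with matched-set effects. Include log(number of weeks observed) as an offset where stores differ in weeks of data. The pre-intervention and intervention dates as printed span 91 and 78 days, but a difference in length common to all stores cancels between the arms. Report the ratio with standard errors clustered by store ID, which also covers control stores used in more than one set.
- **Baseline.** State that it enters as log(pre-period sales), with a rule for a store that sold none of a product. This improves precision and reduces, but may not remove, bias from any baseline difference within sets.
- **Revenue.** Use a log-link quasi-likelihood, such as Poisson quasi-likelihood with matched-set effects and the same clustered standard errors. It accepts non-integer values, and its inference is the same in pounds and pence. Other scale-free choices would also serve.
- **Wording.** Delete the statement that the average is a count. The average can remain as the descriptive summary.

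The weekly store rows requested in Annex A already supply the data. The cost is one paragraph and a few lines of code. If the planned model has already been fitted, report both and date the change.

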## Study design

A non-randomised controlled before and after study comparing sales/purchasing data in 20 supermarket stores delivering the intervention and a matched sample (provisionally 1:5) of control stores. The intervention will be implemented by stores in the week beginning 27 January 2019. The set-up period (the first week) will be excluded from the analysis of sales.

The study will compare changes in sales of meat and meat-free alternatives in the intervention and control stores across two 12-week time periods: a pre-intervention comparison period (2 September 2018 to 1 December 2018 and the intervention period (3rd February 2019 to 21 April 2019). Subject to data availability, an interrupted time series analysis will also be conducted to evaluate changes in weekly sales of meat and meat-free alternatives associated with the intervention.

The pre-intervention and intervention periods have been selected by the retail partner to avoid months where meat purchases are known to be atypical (e.g. Christmas, 'Veganuary' and summer 'barbeque season').

The impact of the intervention will be evaluated using aggregated weekly store level sales data.

A further evaluation may be conducted using anonymised individual-level purchasing data derived from the retail partner's loyalty card data. This will be covered by a separate protocol.

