## Selection of control stores

The retail partner uses proprietary analytics software to select control stores based on individual – level purchasing data captured by their loyalty card scheme. The software is designed to select control stores based on the following data from up to 104 weeks preceding the intervention on: the store format, and, for the selected product group the seasonal sales trend, sales, visits per customer, spend per visit and customer affluence. The software is designed to identify control stores which have a similar purchasing pattern to the intervention stores.

For this study, the software was used to identify 5 matched control stores for each intervention store, based on store customers' patterns of purchase of meat-free alternatives over the 52 weeks preceding the intervention period. A 52 week period rather than 104 weeks was used by the retail partner because the purchasing pattern of meat-free alternatives is undergoing rapid change. The

software does not require all control stores to be unique so stores may be selected as control stores for more than one intervention store.

The research team does not have access to the full details of this matching procedure (since these are confidential), but the suitability of the control sample will be assessed prior to undertaking the main analysis of outcome data (see below). Of particular note, the matching procedure does not explicitly require control stores to have 'baggy' space in the MFP aisle so it will be necessary to verify that the control stores have similar purchasing trends in the pre-intervention period for both meat and meat-free alternatives. If necessary, the selection and matching procedures for the control stores may be modified e.g. removing duplicate control stores from the analysis. Any such changes will be fully documented prior to the main analysis.

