### Preliminary analysis of pre-intervention data

The following preliminary analyses will be conducted using the data listed in Annex A, blinded to the outcome data:

**Time trends:** We will plot time trends in the study outcomes, by store and overall (intervention vs control) for up to 25 months preceding the start of the intervention. Subject to data availability we will plot weekly sales data. If weekly data are not available we will examine trends by comparing sales data for the time periods January-March 2018 and September-November 2018 and, if possible for the same periods in 2017 i.e. periods corresponding to the study intervention and pre-intervention comparator periods.

We will visually inspect these plots to assess whether time trends are broadly similar in the intervention and control stores and whether there is any evidence of systematic differences by store characteristics, using the store classification data provided by the retail partner. These data include affluence (more affluent, average, less affluent), customer age (younger, older), ethnic mix (White, Asian, Other) and population density (more urban, urban, less urban). Outliers may be investigated.

**Propensity to reduce meat purchases and/or switch to meat-free alternatives** We will compute a range of store-level measures designed to capture propensity to reduce meat purchase and increase purchases of meat-free alternatives. These will include: change in sales of meat and meat-free alternatives in 'Veganuary' relative to sales in other periods. We will visually explore whether these outcomes appear to differ between intervention and control stores and whether these measures appear to differ by store characteristics.

The data required to conduct these preliminary analyses are summarised in annex A.

Based on these preliminary analyses we will specify and document the variables that are potential confounders.

If time trends appear to differ between the intervention and control stores, we may define a subgroup of stores which we consider to have comparable sales time trends, prior to commencing analysis of the main outcomes.

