## Annex A: Specification of pre-intervention exploratory dataset, main analysis dataset, and list of store characteristic variables

### Sales data

1. **Exploratory pre-intervention dataset:** Weekly store-level sales data for the time period January 2017 - January 2019 (inclusive).
2. **Main analysis dataset:** as above but including the intervention period (February – April 2019)

Each row of the dataset to contain data for one week for a single store (or other format to be agreed)

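### The outcome model's only sales baseline is autumn 2018, a different season from the February-April 2019 outcome, although Annex A already specifies the same stores' February-April 2018 sales.

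*Protocol*

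**What the plan says.** Study design (Protocol) compares two periods, "2 September 2018 to 1 December 2018 and the intervention period (3rd February 2019 to 21 April 2019"). They "have been selected by the retail partner to avoid months where meat purchases are known to be atypical", the examples given being Christmas, Veganuary and the barbecue season. Analysis strategy tests for differences between arms "adjusted for differences in sales volume during the pre-intervention comparator period". Statistical methods specifies "conditional negative binomial regression adjusted for the covariates (store characteristics) and also the baseline count (pre-intervention period sales"). Store characteristics identified as potential confounders are the only other covariates.

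Annex A (Sales data) defines an exploratory dataset of "Weekly store-level sales data for the time period January 2017 - January 2019 (inclusive") and a main analysis dataset that is "as above but including the intervention period (February – April 2019"). February-April 2018 therefore lies within the specified data for every store.

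Selection of control stores says the retailer's software can use the seasonal sales trend of the selected product group. For this study that group was meat-free alternatives, with patterns taken "over the 52 weeks preceding the intervention period". The primary outcome is total units of meat mince, burgers, meatballs and sausages.

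**The concern.** Avoiding atypical months does not make September-November and February-April the same season. Each store has its own ratio of spring to autumn meat sales. A model with only an autumn baseline has no information on that ratio beyond what the matched set and the store characteristics carry. Two things follow.

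- Store-to-store variation in the ratio becomes residual noise.
- If intervention stores differ from their controls in the ratio on average, the unexplained part of that difference is estimated as an intervention effect on the primary outcome.

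A difference is plausible. Intervention stores had to have excess display space in the meat, fish and poultry aisle, controls did not, and the matching looked at another product group. The protocol itself says similar pre-intervention trends still have to be verified for both meat and meat-free products.

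**Working it through.** **No figure to reproduce.** The protocol gives no variance, effect size or power. The SDs and arm differences below are assumptions. Only the design of 20 sets of one intervention store and five controls comes from the documents.

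**Dates.** 2 September to 1 December 2018 is 91 days, or 13 weeks. 3 February to 21 April 2019 is 78 days, or 11 weeks and 1 day. Both are called 12 weeks.

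**Model, log scale, in per cent.** Store sales = level + seasonal effect in spring (SD s) + half-yearly random-walk drift (SD d) + period noise (SD e = 1). Spring 2019 is regressed within sets on arm and autumn 2018, with or without spring 2018. Set effects stand in for the conditional negative binomial model; controls are taken as unique and there are no store covariates.

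If store levels vary much more than the other terms, the baseline coefficients sum to about 1. The result then depends on two changes:

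- spring 2019 minus autumn 2018, with variance V = s² + d² + 2e²;
- spring 2018 minus autumn 2018, with the same variance V and covariance C = s² + e² with the first.

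Write k = C/V. The design factor is (1/20)(1 + 1/5) = 0.06. Then:

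- SE, autumn only = √(0.06 V)
- SE, both baselines = √(0.06 V (1 − k²))
- bias from an arm difference of 3 in seasonal swing: 3 with autumn only, 3(1 − k) with both.

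Formula values are shown first, with simulated values (3,000 runs per setting) in brackets.

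| s / d | V | k | SE autumn only | SE both | Bias left of 3.0 |
|---|---|---|---|---|---|
| 2 / 4 | 22 | 5/22 = 0.227 | 1.15 (1.16) | 1.12 (1.14) | 2.32 (2.33) |
| 3 / 3 | 20 | 10/20 = 0.500 | 1.10 (1.10) | 0.95 (0.95) | 1.50 (1.50) |
| 4 / 4 | 34 | 17/34 = 0.500 | 1.43 (1.44) | 1.24 (1.26) | 1.50 (1.51) |
| 4 / 2 | 22 | 17/22 = 0.773 | 1.15 (1.15) | 0.73 (0.73) | 0.68 (0.68) |
| 5 / 3 | 36 | 26/36 = 0.722 | 1.47 (1.47) | 1.02 (1.04) | 0.83 (0.83) |

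The simulated SE falls by 1 − 1.14/1.16 = 2% in the first row and by 1 − 0.73/1.15 = 37% in the fourth. The rows between give 14%, 12% or 13% (1.44 to 1.26 is 12.5%) and 29%.

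**Wider assumptions.** A second simulation used season SD 2-10%, noise 2-3% and yearly growth SD 0-5%. With no arm difference, the false-positive rate of the autumn-only model stayed near 5% (4.6-5.4%), so the only cost was precision. With a 2% arm difference in swing it was 11-64%, against 5-23% with spring 2018 added.

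**Where the extra covariate does not help.** Suppose the arms differ instead by a steady growth g per half-year. The first change then differs by g between arms and the second by −g, so the bias is g with autumn only and g(1 + k) with both. For g = 1 that is 1.00 against 1.23-1.77 over the rows above. If the second covariate is the store's change from autumn 2017 to spring 2018, its slope is k′ = s²/V, which is 0.18-0.73. The bias is then g(1 − k′), or 0.82-0.27, and 3(1 − k′), or 2.45-0.82, remains from a 3% seasonal difference.

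**The case against.** **The protocol already looks at this risk.** Preliminary analysis of pre-intervention data plots up to 25 months of trends, blinded to outcome. Its fallback reads "If weekly data are not available we will examine trends by comparing sales data for the time periods January-March 2018 and September-November 2018", which is the right seasonal contrast. Fish and non-dairy milk are analysed first, and an interrupted time series is planned subject to data availability. This stands as evidence that the risk was seen. But the checks are visual, and they lead to a list of confounding store characteristics and an optional subgroup. The control products need not share the seasonality of mince or sausages. The time series is conditional on data and is not the main analysis. None of these changes the main model.

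**Covariate lists usually belong in the analysis plan.** That is true of details, but this protocol states which sales period is the baseline, and does so consistently in three sections.

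**Matching handles season.** A reader might go further the other way and infer that the 52-week matching window cannot help because it contains spring 2018 followed by autumn 2018 and no autumn-to-spring change. The documents do not support that. Seasonal trend is a listed input to the software, and if seasonality is stable, spring-to-autumn 2018 carries the information. The proposed covariate relies on exactly that. The sound reason to doubt the matching is that it used meat-free purchasing.

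**The size is assumed.** This stands in full. At a season SD of 2% and drift of 4% the gain in precision is negligible and most of the bias remains.

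**Conclusion.** The point holds as a recommended improvement to a stated model. Autumn 2018 is the only sales baseline for a spring 2019 outcome, and the same stores' spring 2018 sales are specified but unused in that model. Under the assumed SDs the standard error falls by about 2% to 37%, and bias from a 3% arm difference in seasonal swing falls from 3.0% to 0.7-2.3%.

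A reader might infer that the planned estimate is biased, or that any seasonal difference counts in full. Neither follows. Nothing in the documents shows that the arms differ in seasonality, and only the part left by matching and store covariates would pass through. The full 3.0% above reflects a calculation without store covariates. Nor is the extra covariate a remedy for every imbalance: it addresses seasonal swing, and it enlarges the bias if the arms differ in steady growth.

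**What to change.** In Statistical methods, add a second log-scale covariate to the main model: each store's mean weekly sales of the same outcome over the 2018 calendar weeks corresponding to the intervention window. Enter the autumn 2018 baseline on the log scale as well. Apply the same model to fish and non-dairy milk. First reconcile the two periods called 12 weeks in Study design with their dates, because the 2018 weeks cannot be defined until then.

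As a sensitivity analysis, replace the second covariate with the store's change from autumn 2017 to spring 2018, where those data are supplied. A marked disagreement between the two models would point to differing growth rather than differing seasonality.

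Weekly data are subject to availability. If they are not supplied, request the total for the matching 2018 period, since the January-March fallback includes Veganuary and omits April.

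The cost is one degree of freedom (about 100 within sets if the controls are unique, which the protocol does not guarantee) and a line or two of wording. The benefit is smaller for meat-free outcomes, where the protocol describes purchasing as changing rapidly and some of the 26 lines may not have been on sale in spring 2018.

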## Selection of intervention stores

The criteria for selecting the intervention stores were set by the retail partner's finance and data teams. To be eligible, intervention stores needed to be supermarkets with excess display bays in the MFP aisle whose inventory volume was not justified by sales or customer volume ('baggy space'). For this pilot study, 20 supermarkets were selected based on a pragmatic balance between the benefits of including more stores in the evaluation with the potential risk of lost sales revenue.

The stores were selected to have a broad spread with regard to the following store characteristics:

- Affluence (based on top 2 Acorn consumer classification categories [10] within 10 minutes' drive, in combination with meat free sales performance (assessed in the 12 week period ending 25 September 2018)
- Store size (Large, Medium, Small, 'Local')

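### If control stores are shared between matched sets, the main analysis counts the same store several times and its 95% confidence interval is too narrow

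*Protocol*

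**What the plan says.** The section Selection of control stores states that "the software was used to identify 5 matched control stores for each intervention store". It adds that the "software does not require all control stores to be unique so stores may be selected as control stores for more than one intervention store". It also permits duplicates to be taken out before the main analysis if this proves necessary, provided the change is documented beforehand.

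Analysis strategy states: "The main analysis will be conducted using all intervention and control stores". Statistical methods then gives the rule for shared controls: "In the event that some stores are selected as control stores for multiple intervention stores, we will run the analysis on the full dataset". The same sentence adds a sensitivity analysis to see whether the sharing matters. The next sentence allows duplicates to be dropped and the analysis repeated on distinct controls where that is judged appropriate.

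On dependence between observations, Statistical methods says only this: "We will use conditional regression to account for the matching of stores". The main model is described as follows: "Multivariate analysis will be conducted using conditional negative binomial regression adjusted for the covariates (store characteristics) and also the baseline count". The protocol mentions no store-level cluster, robust variance, store effect or weight. Annex A lists both the store's own ID and a store group, which is the ID of the intervention store it is matched to. A shared control can therefore appear under several groups with identical sales.

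**The concern.** Conditioning on the matched set removes what the stores in one set have in common. It does not remove the correlation between two sets that contain the same control store. If that store happens to sell unusually much or little in the intervention period, every set that uses it shifts in the same direction. A likelihood that treats the sets as independent reads this as repeated evidence and understates the standard error.

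The primary outcome is judged by a 95% interval and a 5% test, and the study is also meant to supply effect estimates for later work. An interval that is too narrow could make a chance difference in meat sales look established. Sharing does not by itself bias the point estimate. The error is in the stated precision.

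**Working it through.** **Inputs**
- Intervention stores: 20 (Selection of intervention stores: "20 supermarkets were selected based on a pragmatic balance").
- Controls per intervention store: 5 (Selection of control stores), so 20 × 5 = 100 control slots.
- Level: "all statistical tests will be conducted at a 5% significance level" (Statistical methods). I take it as two-sided because 95% intervals are reported, so z = 1.960.
- Number of distinct control stores, U: not stated. I vary it from 100 (no sharing) to 20.

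The protocol has no power calculation, so the nominal 5% is the only figure to reproduce.

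**Formula.** Assume that each store's residual, on the log scale after adjustment, has variance s² and is independent of other stores' residuals.
- Variance the model assumes: s²(1/20 + 1/100) = 0.06 s².
- True variance when control j fills k_j slots: s²(1/20 + Σk_j²/100²).
- Equal sharing, k = 100/U: Σk²/100² = U × (100/U)²/100² = 1/U.
- Ratio of true to reported standard error: r = √[(1/20 + 1/U)/0.06].
- True type I error: 2[1 − Φ(1.960/r)].

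**Results, equal sharing**

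| U | 1/20 + 1/U | r | Interval too narrow by (1 − 1/r) | Type I error |
|---|---|---|---|---|
| 100 | 0.0600 | 1.00 | 0% | 5.0% |
| 80 | 0.0625 | 1.02 | 2.0% | 5.5% |
| 50 | 0.0700 | 1.08 | 7.4% | 7.0% |
| 25 | 0.0900 | 1.22 | 18.4% | 11.0% |
| 20 | 0.1000 | 1.29 | 22.5% | 12.9% |

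With U = 100 the formula returns the nominal level, as it should.

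**Uneven sharing (illustration).** Take 35 distinct controls: five used 10 times, twenty used twice and ten used once. The slots add up to 50 + 40 + 10 = 100, and Σk² = 500 + 80 + 10 = 590. The variance is 0.05 + 0.059 = 0.109, r = √(0.109/0.06) = 1.35, and the type I error is 14.6%. The same 35 controls used equally would give 0.05 + 1/35 = 0.0786, r = 1.14 and 8.7%.

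**Simulation check under no effect**
- A negative binomial regression with set effects and log baseline, used as a stand-in for the conditional model (1,500 runs each), rejected in 3.9% with U = 100, 7.7% with 50, 11.5% with 25 and 13.2% with 20.
- A linear model with set effects and nearest-neighbour matching (4,000 runs each) gave 4.8% with no sharing. It gave 5.0% at a mean U of about 88, 5.9% at 78, 7.3% at 62, 9.3% at 48, 10.4% at 36 and 15.2% at 24.

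Both agree with the formula in direction and approximate size. The second runs higher at low U, where nearest-neighbour matching makes sharing uneven.

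**Check of the obvious remedy.** In the linear simulation, a plain variance clustered on store, with a t reference on 19 degrees of freedom, rejected in 6.5% to 8.0% whatever the amount of sharing, including 6.9% with none. It stops the error from growing with sharing, but it is itself too liberal with only 20 treated stores.

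**The case against.** Several points can fairly be made in the plan's defence.

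*Sharing is a possibility, not a reported fact.* This stands. A reader might infer that the primary interval is wrong as it is now written. The protocol does not support that, because it says only that sharing may happen and never gives its extent. With 80 distinct controls the interval is 2.0% too narrow, which is negligible.

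*The authors saw the issue.* This also stands. A reader who stops at the instruction to use the full dataset might infer that nothing further is planned. In fact a sensitivity analysis follows, and duplicates may be removed either before the main analysis or in a re-run. These steps do not repair the main result, however. A sensitivity analysis leaves the primary interval as it was. Removal has no criterion, the re-run could be decided after the full-data result is known, and no rule says which set keeps a shared store.

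*The variance estimator is commonly left to a statistical analysis plan, and none is at hand.* This stands in part. The text does not exclude a store-clustered variance. But the protocol itself fixes the dataset, the model and the one source of dependence to be handled, and it foresees shared controls without attaching any variance correction to them.

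*The study calls itself a pilot.* This lowers the urgency. It does not remove the point, because a primary outcome, 95% intervals and 5% tests are specified.

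**Conclusion.** The point holds conditionally. Whenever control stores are shared between sets, the main analysis as described understates the standard error, and the 5% test is anti-conservative. Under equal sharing the true type I error runs from about 5.5% (80 distinct controls) through 7.0% (50) and 11% (25) to 13% (20). Uneven sharing makes it worse, but the 14.6% case is an invented pattern and not an estimate for this study.

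These figures assume a model-based variance, equal residual variance across stores and independence between different stores. The extent of sharing is unknown, so the real error could be trivial or material. This should be settled before the results are interpreted, but it does not invalidate the study.

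**What to change.** In Statistical methods, fix one rule for the main analysis. Either option below would do.
- Keep the matched sets and use a variance clustered on Store ID, which Annex A already lists, with a small-sample correction. The plain clustered variance is not enough, as the simulation shows.
- Enter each physical store once, weighted for the sets it serves. The weight must not be treated as a frequency, since that would bring back the same error. The text must also say how the matching is then handled.

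Report the number of distinct control stores and how often each is used. Keep deletion of duplicates as a sensitivity analysis, with a rule stated in advance for which set keeps a shared store. Align the section Selection of control stores with this, so that the same rule governs removal before and after the main run.

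The cost is a few sentences and a somewhat more careful variance calculation, with no new data. If sharing is light, little changes. If it is heavy, the standard error grows by the ratio r above, for example by 22% with 25 distinct controls used equally.
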